## Abstract

**Background:**

Obstructive sleep apnea (OSA) occurs due to sleep-induced upper airway muscle relaxation resulting in increased pharyngeal collapsibility. Clinical trials have shown a favorable effect of exercise training on OSA severity in middle-aged adults. Aging is characterized by motor-unit loss. Force training may affect the whole body muscle tone. We hypothesize that interventions increasing muscle strength might propagate to motor units at the abductor pharyngeal muscles, reducing collapsibility and, hence, sleep apnea severity in elderly patients with obstructive sleep apnea.

**Methods/design:**

This is a randomized clinical trial including patients between 65 and 80 years of age, with obstructive sleep apnea, and an apnea-hypopnea index (AHI) between 20 and 50 events/hour, diagnosed by out-of-center in-home type III polysomnography. Forty subjects will be included and randomly assigned to two equal sized groups. The participants allocated to the intervention group will attend two sessions per week of one-hour strength training for the legs, arms, chest, back, and abdomen and the controls will receive advice on lifestyle change. The primary outcome measure of the study will be the change in apnea-hypopnea index and the secondary outcomes will be the body composition, evaluated by anthropometric and bioelectrical impedance variables; maximum dynamic force, appraised by one-repetition maximum strength test; muscle quality and thickness by ultrasound; physical function assessed by sit-to-stand test, timed up and go test, handgrip strength test. The study duration will be 12 weeks. Intention-to-treat and per-protocol analyses will be performed.

**Discussion:**

The high prevalence of obstructive sleep apnea in elderly people is a public health issue. OSA is a recognized cause of cardiovascular disease and reduces quality of life due to sleepiness and fatigue. Exercise is a low-cost intervention that could help to detain the trend towards age-dependent loss of pharyngeal motor units and progressive severity of obstructive sleep apnea. Home-based strength exercises may represent a more practical approach than aerobic exercise for elderly patients. If the results confirm our hypothesis, further research on the clinical application of our findings will be warranted.

**Trial registration:**

ClinicalTrials.gov, NCT02742792. Registered on 1 April 2016.

**Electronic supplementary material:**

The online version of this article (doi:10.1186/s13063-017-2238-3) contains supplementary material, which is available to authorized users.

## Background

Obstructive sleep apnea (OSA) causes repeated surges of hypoxia and awakenings during sleep [1]. OSA occurs in up to one third of the population [2], constituting a public health problem [3]. The prevalence of sleep apnea increases with age. In young women, the prevalence is 1.4%. In both men and women 70 years or older, it reaches 90% and more [2, 4]. This remarkable increase in prevalence is explainable, at least in part, by escalating body weight with age, but several contributing factors, which deserve medical attention, should be considered.

The repeated arousals caused by the need to restore breathing after each one of the recurrent breathing interruptions have as a consequence sympathetic hyperactivity, somnolence, and fatigue. Intermittent hypoxia is associated to oxidative stress, inflammation, and cardiovascular impairments [5]. Periods of sleep-dependent hypoxia also cause motor cortex dysfunction [6] Intermittent hypoxia was shown to cause demyelination [7] and neuronal damage, notably in the cerebellum [8]. In addition, OSA is a risk factor for hypertension [9], coronary artery disease [10] , heart failure [11], and arrhythmias [12].

Treatment options for OSA are several and the most effective is the use of a continuous positive airway pressure (CPAP) device [13]. Oral appliances for mandibular advancement [14, 15], surgery [16], weight reduction, and lifestyle change, including recommendation of regular exercise [17] are alternatives to CPAP.

Physical exercise is accepted culturally and scientifically as a non-pharmacological intervention beneficial to health [18, 19]. Aerobic and resistance training improves general wellbeing and particularly sleep quality [20, 21]. A sedentary lifestyle is linked with higher prevalence and severity of sleep apnea. On the other hand, exercise gives consistent results in treating OSA, and increasing the number of hours of exercise is associated with reduction in the severity of OSA [22, 23].

In experimental studies, the effect size of exercise in the treatment of OSA ranges between 0.6 [24] and 1.5 [25] standard deviations. In a meta-analysis of five studies, totaling 129 participants, the mean effect is a reduction of seven events per hour [26]. All randomized clinical trials and other studies have involved participants between 42 and 54 years of age on average. No study involving the most affected population, elderly individuals, was identified in extensive PubMed and Embase searches. The decrease in physical fitness in the elderly is associated with motor unit loss [27, 28], falls [29, 30], pain [31], musculoskeletal changes, and sleep disorders [32, 33]. Moreover, the worsening of overall physical function is a predictor of mortality [34].

The relevance of strength training in elderly people is linked to the medical consequences of muscle fiber loss. Sarcopenia starts at the age of 35 years and 45 years, in men and women, respectively [35–37], and progresses at a rate of 1–2% per year after the sixth decade [38]. It is aggravated by sedentary lifestyle, reduced levels of trophic hormones, and neurodegenerative processes [39, 40]. It is plausible that weakening of the pharyngeal abductor muscles participates in the age-related increase in the prevalence of OSA. Hypothetically, a widespread tonic effect [41] could lead to improvement in pharyngeal abductor function, bettering airway patency during sleep.

The increase in OSA prevalence with ageing may be linked also to overnight rostral fluid displacement from the legs [42]. Leg fluid volume correlates with the apnea-hypopnea index (AHI) and with the number of hours sitting, suggesting that “a sedentary way of life may predispose to OSA” [43].

Despite the abundant evidence on the effects of resistance training on the neuromuscular function, the issue of deleterious effects of OSA on muscle function in elderly subjects remains uninvestigated. Moreover, no high-level evidence on the effects of strength training on the severity of OSA in elderly people was found.

### Rationale

The systemic improvement in muscle strength after resistance training may reach the abductor pharyngeal muscle and improve OSA. Hypothetically, a widespread tonic effect would lead to an improvement in pharyngeal abductor function and bettering of airway patency during sleep. Also, reduction in sedentarism may reduce fluid retention. Reduction in the severity of OSA induced by physical training has been shown in randomized clinical trials and meta-analyses, but none of the studies to date have investigated the effect of strength training on sleep apnea severity in elderly individuals.

### Research question

Will elderly people performing resistance training reduce the AHI in comparison with a control group performing recreational physical activity?

## Methods/design

### Study design

This study is a parallel randomized, blind, controlled superiority trial. The study strategy is registered, constructed and presented according to the recommendations for interventional trials [44] (see Additional file 1 for the Standard Protocol Items: Recommendations for Interventional Trials (SPIRIT) checklist).

#### Eligible participants

##### Inclusion criteria

Patients should fulfill the following criteria:Age between 65 and 80 yearsEither genderNot being engaged in regular structured resistance exerciseAHI between 20 and 50 events per hourAvailability of time to include physical activity in their routineConsenting to participate in the survey

##### Exclusion criteria

Being in treatment for sleep apneaOsteoarticular injuries or illnesses that impair the performance of the exercises included in the projectNeuromuscular problemsUncontrolled hypertensionAcute myocardial infarction or stroke in the last yearRecent trauma to the upper airwayOther serious chronic disease with treatment for over a month in the last yearRegular or abusive use of medications or drugs with effects on the central nervous system

### Sample size

The sample size calculation for this trial was performed using the G-Power program (Franz Faul, Universität Kiel, Germany) [45]. We chose an effect size of 0.6 standard deviations described as the lowest among five articles included in a meta-analysis of the effect of exercise studies on sleep apnea [24] as the target for our study. For two groups (training and control) and two assessments (before and after 12 weeks of training), with 90% power and probability of alpha error of 5%, the sample size calculated for analysis of variance with repeated measures would be 16 patients in each group. To compensate for possible participant loss, 40 subjects will be included. Losses after randomization will be included in the intention-to-treat but not in the per-protocol analyses.

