## Discussion

The present study is designed to evaluate the effects of resistance training on OSA severity in elderly persons. Our hypothesis is that resistance training will reduce OSA severity while improving neuromuscular function. A previous systematic review and meta-analysis showed that exercise training reduces approximately seven events in AHI compared to control groups [24]. However, little is known about the effect of resistance training alone without aerobic training on OSA in the elderly population. Also, the efficacy of this intervention remains untested in elderly populations, possibly because of prejudices about age-related frailty. None of the studies found in an ample PubMed and Embase search mentioned any randomized controlled trials (RCTs) of treatments for OSA

Resistance training is recognized as the most effective intervention to improve the muscle mass and quality, i.e., lean muscle mass, quadriceps muscle thickness, and intramuscular adipose tissue. Also, resistance training enhances the neuromuscular function, i.e., lower limb strength, and specific tension in elderly persons [67]. To the best of our knowledge this would be the first study to investigate the heterotopic effect of resistance training. Regarding the secondary outcomes, the enhancements of performance in functional tests have seldom been described in elderly people [68]. Therefore, our RCT will provide data for analyses of the relationship between OSA and functional performance.

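### The stated 90% power for a 0.6 SD effect with 16 per group does not follow for the between-group difference in AHI change unless the pre-post correlation is about 0.87, and no correlation is stated

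*Protocol article*

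**What the plan says.** Sample size section: "We chose an effect size of 0.6 standard deviations described as the lowest among five articles included in a meta-analysis" of exercise studies, and this is the target. With two groups, two assessments, 90% power and 5% alpha, "the sample size calculated for analysis of variance with repeated measures would be 16 patients in each group". Enrolment is raised to 40 (20 per group) to allow for losses. The section does not give the pre-post correlation, and it does not say whether 0.6 is in units of the SD of AHI or the SD of its change.

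Three other places show that the target is a treatment effect, exercise against control:

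- Background: "the effect size of exercise in the treatment of OSA ranges between 0.6 [24] and 1.5 [25] standard deviations".
- Discussion, on the meta-analysis: "exercise training reduces approximately seven events in AHI compared to control groups".
- The Research question is a comparison with a control group, the Abstract makes the change in AHI the primary outcome, and Statistical methods tests group differences and the time-by-group interaction by generalized estimating equations.

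**The concern.** Read together, these sections claim 90% power to detect a 0.6 SD difference between the groups in AHI change. Sixteen per group is very few for that; an ordinary two-sample comparison at 0.6 SD needs several times as many.

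A likely explanation is a conversion slip. Halving a standardised difference (f = d/2) is right for comparing two group means. It is not right for a two-by-two interaction, where the same difference in change corresponds to half that f.

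The article chose the lowest of the published effects as its target, so a reader will take the trial as well powered even for a modest benefit. If the real power for that target is far lower, a non-significant result could be read as evidence against strength training when the trial had a large chance of missing the effect it was sized for. The Background says no earlier study in elderly patients was found, so there is little else to correct that reading.

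**Working it through.** **Inputs from the article.** Effect 0.6 SD; power 90%; alpha 5%; two groups by two assessments; 16 per group calculated (N = 32), 20 per group enrolled.

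**Assumed, because not stated.** Two-sided test; pre-post correlation ρ, shown over a range; equal SDs before and after.

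**1. Reproducing 16 per group.** The repeated-measures routine for the within-between interaction uses noncentrality λ = f² × N × m / (1 − ρ), with m = 2 and degrees of freedom 1 and N − 2. Take f = 0.6/2 = 0.3 and ρ = 0.5:

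- N = 30: λ = 0.09 × 30 × 2 / 0.5 = 10.80, power 88.7%.
- N = 32: λ = 0.09 × 32 × 2 / 0.5 = 11.52, power 90.7%.

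The smallest N that reaches 90% is 32, which is the stated 16 per group.

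**2. What f = 0.3 means here.** If the groups differ by δ in their change, each of the four interaction cell effects is ±δ/4, so f = δ/(4 SD). Then f = 0.3 gives δ = 1.2 SD. A two-sample t test on change with d = 1.2 (at ρ = 0.5 the SD of change equals the raw SD) confirms it: noncentrality 1.2 × √(16/2) = 3.394, whose square is 11.52, with the same power of 90.7%.

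**3. Power for the declared 0.6 SD.** Now f = 0.6/4 = 0.15. At ρ = 0.5 and N = 32, λ = 0.0225 × 32 × 2 / 0.5 = 2.88.

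- 16 per group: 37.6% (37.3% in a simulation of 40,000 trials).
- 20 per group: 45.6%.
- 90% power needs 60 per group.
- Difference detectable with 90% power: 1.18 SD with 16 per group, 1.05 SD with 20.

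If 0.6 is in units of the SD of change, these figures hold whatever the correlation.

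**4. If 0.6 is in units of the raw AHI SD.** SD of change = SD × √(2(1 − ρ)), so the standardised difference in change is 0.6/√(2(1 − ρ)).

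| ρ | Standardised difference | Power, 16 per group | Power, 20 per group |
|---|---|---|---|
| 0.3 | 0.507 | 28% | 35% |
| 0.5 | 0.600 | 38% | 46% |
| 0.7 | 0.775 | 56% | 67% |
| 0.8 | 0.949 | 74% | 83% |
| 0.875 | 1.200 | 91% | 96% |

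For 90% with 16 per group: 2(1 − ρ) = (0.6/1.185)² = 0.256, so ρ is about 0.87.

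**5. Other readings of 0.6 SD, 16 per group.** A one-sided t test on change gives 50.5%. A between-factor test with f = 0.3 and ρ = 0.5 gives 47.5%. A baseline-adjusted comparison gives 47.5% at ρ = 0.5 and 78% at ρ = 0.8, though Statistical methods names no baseline covariate. A paired t test of a 0.6 SD pre-post change in all 32 patients pooled gives 90.8%, but that ignores the randomised comparison.

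**The case against.** The strongest reply is that the answer depends on inputs the article does not give. With a raw-SD effect and a high enough correlation, 16 per group is correct: at 0.875 power is 91%. This stands as a limit on how the point may be put. A reader might infer that power is 38% without qualification, or that 16 per group can only ever detect 1.2 SD. The documents do not support either; both hold in SD-of-change units or at correlation 0.5.

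It is also fair to say that f = 0.3 and ρ = 0.5 are worked back from the answer. The within-factor routine gives the same N, so the routine actually run cannot be identified. The exact match is good evidence of how 16 arose, but it is not proof. The conclusion does not need it, because steps 3 to 5 start from the declared 0.6 SD.

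A reader might go further and say that a correlation of 0.87 is impossible with one recording per occasion and entry limited to an AHI of 20 to 50. Restricting the range tends to lower correlation, but the article gives no repeatability figure for AHI, so that cannot be asserted from it. It is enough that the needed value is neither stated nor supported.

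Finally, a journal article condenses its protocol. That excuses an unstated correlation taken alone. It does not excuse a printed effect size, power and sample size that fail to agree at any moderate correlation.

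**Conclusion.** The power claim is wrong as written. For a 0.6 SD between-group difference in AHI change at two-sided 5%, 16 per group falls well short of 90% on every reading tried of the randomised comparison at correlations from 0.3 to 0.7. The 20 per group enrolled as a loss allowance do not close the gap over that range.

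It would be too strong to say that the trial is more likely than not to miss a 0.6 SD effect. That holds at correlation 0.5 and below, and in SD-of-change units, but in raw-SD units at correlation 0.7 power is above one half. Nor does the finding show that the trial needs 60 per group; that is the requirement at correlation 0.5 or in SD-of-change units.

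The size in events per hour cannot be given, because the article reports no AHI SD. At correlation 0.5, 1.2 SD exceeds the meta-analytic effect cited in the Background ("the mean effect is a reduction of seven events per hour") whenever the SD is above 7/1.2 = 5.8.

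**What to change.** Correct the Sample size paragraph. State which SD the 0.6 refers to and what pre-post correlation is assumed, and replace the power claim with wording such as:

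> Sixteen per group gives 90% power for a between-group difference in AHI change of about 1.2 SD (two-sided 5%, correlation 0.5). For 0.6 SD, power is about 38% with 16 and 46% with 20 per group. If 0.6 is in units of the raw AHI SD, power with 16 (20) per group is 28% (35%), 56% (67%) and 74% (83%) at correlations 0.3, 0.7 and 0.8. A non-significant result does not exclude a 0.6 SD effect.

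If the investigators did assume a correlation near 0.87, they should say so and give its source.

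No change in enrolment, which Trial status describes as ongoing, is asked for, and no procedure or analysis changes. The cost is one reworded paragraph and a less favourable stated power.

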### Randomization process

Randomization will be performed using a sequence of numbers generated by computer at randomization.com. Patients will be assigned to the intervention or control groups by a researcher with no information about the participants and not otherwise involved in the protocol.

### Blinding

The evaluators taking measurements for outcomes will be blinded to the group assignment. The physical educator responsible for prescribing and monitoring the training will not be blinded to the groups and will not be involved in other steps of the protocol. A certified scorer blinded to the groups will perform the scoring of the AHI. The blinding code will be broken at the end of the study or earlier by request of regulatory committees or in the case of serious adverse events in connection with the group assignment.

### Recruitment

The information technology system of the university hospital will generate a list of patients aged 65 to 80 years ascribed to the institutional primary care unit. After chart review, the subjects will be invited to join in the study through telephone calls. Those willing to participate will visit the institutional research center to undergo the informed consent process and initiate the assessment.

### Statistical methods

Intention-to-treat and per-protocol analyses will be performed for the primary and secondary outcomes. Patients who do not perform the 24 training sessions or who report poor adherence to the healthy lifestyle program during 2 weeks or more will be excluded from the per-protocol analysis. Missing data will be considered as missing, without data imputation.

Means and standard deviation will be used to represent data with a normal distribution and medians and quartiles will be used to describe non-normally distributed data. Natural logarithm transformation will be used before inclusion of non-normally distributed dependent variables in analyses. The significance of the differences between groups, at the baseline, will be tested by the Student *t* test and chi-squared test, for linear and categorical variables, respectively. Generalized estimating equations (GEE) will be used to detect differences between exercise and control groups and time*group interaction. The results with *P* values <0.05 for alpha error will be considered statistically significant. Statistical analyses will be performed using SPSS software (SPSS Inc., Chicago, IL, USA).

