### Monitoring

Monitoring of the physical activity in the intervention group will be performed by the physical educator after each session in a specific form of the electronic case report form. Patients in the control group will record in a log sheet the number of goals met during each week. The institutional ethics committee will be monitoring the data. All analyses will be performed at the end of the study.

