### Follow up and duration of the study

There will be four visits at the clinical research center for outcome evaluation. Two will be at baseline (a visit to receive the polygraph device and another visit for carrying out evaluation of body composition, physical function, and muscle strength, function, and quality) and two visits at the final follow up (reassessment of the same parameters). The study protocol consists of 12 weeks of strength training twice a week (24 sessions).

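### The per-protocol rule removes an exercise patient for one missed session in 24 but a control only for two or more weeks of self-reported poor adherence

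*Protocol article*

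**What the plan says.** All places are in the protocol article.

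- **Statistical methods.** Intention-to-treat and per-protocol analyses are planned for the primary and secondary outcomes. Left out of the per-protocol analysis are "Patients who do not perform the 24 training sessions or who report poor adherence to the healthy lifestyle program during 2 weeks or more".
- **Follow up and duration of the study.** Training runs twice a week for 12 weeks, 24 sessions in all. The per-protocol criterion is therefore the complete schedule.
- **Monitoring.** In the exercise arm, "Monitoring of the physical activity in the intervention group will be performed by the physical educator after each session". In the other arm, "Patients in the control group will record in a log sheet the number of goals met during each week".
- **Abstract, Methods/design.** "Forty subjects will be included and randomly assigned to two equal sized groups", so 20 per arm.
- **Sample size.** "We chose an effect size of 0.6 standard deviations". With 90% power and 5% alpha this gave 16 per group, and enrolment was raised to 40 to cover losses.

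The article does not use the term healthy lifestyle program elsewhere. I read it as the control arm's lifestyle advice, the only such component described.

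**The concern.** A per-protocol comparison is useful only if both arms are filtered in a similar way. Here one arm must be perfect and the other need only avoid a sustained lapse. The stricter criterion rests on a staff record made at each session; the looser one rests on what patients report about themselves.

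Two things are at stake. The exercise arm of the per-protocol set could become small, which costs precision. It would also be selected after randomization on perfect attendance. If people who never miss a session are healthier or more motivated than the rest, the comparison with controls is no longer like with like, and the difference could be read as an effect of training. Every primary and secondary outcome is to be analysed this way.

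**Working it through.** **1. The plan's own figure.** For the group-by-time interaction in a repeated-measures ANOVA with two groups and m = 2 assessments, take f = 0.6/2 = 0.3 and a correlation between assessments of 0.5. The correlation is an assumption, as the article states none. The noncentrality is λ = f² × N × m / (1 − ρ). At N = 32 this is 0.09 × 32 × 2 / 0.5 = 11.52 and power is 0.907. The smallest even N reaching 0.90 is 32, so 16 per group reproduces.

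On the change-score scale the same noncentrality satisfies d² × (16 × 16)/(16 + 16) = 11.52, so d = √(11.52/8) = 1.2. The plan's calculation thus implies a difference of 1.2 SD of change. That value is used in step 4.

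**2. Exercise patients retained.** Let p be the probability of attending a session. The documents do not give it, so a range is shown, with sessions treated as independent. The chance of 24 out of 24 is p²⁴.

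| p | p²⁴ | Expected of 20 |
|---|---|---|
| 0.90 | 0.080 | 1.6 |
| 0.95 | 0.292 | 5.8 |
| 0.98 | 0.616 | 12.3 |
| 0.99 | 0.786 | 15.7 |

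To expect the planned 16 of 20, p must be 0.8^(1/24) = 0.991.

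**3. Controls retained.** Let w be the probability of an adequate week, with weeks independent and at most one poor week in 12 tolerated. The chance of staying in is w¹² + 12(1 − w)w¹¹.

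| w | Retained | Expected of 20 |
|---|---|---|
| 0.90 | 0.659 | 13.2 |
| 0.95 | 0.882 | 17.6 |
| 0.98 | 0.977 | 19.5 |
| 0.99 | 0.994 | 19.9 |

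Per-session and per-week adherence are different quantities, so setting equal values side by side is only a guide.

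**4. Power of the per-protocol comparison.** This uses a two-sided t test on change at 5%, with noncentrality d × √(n₁n₂/(n₁ + n₂)) and d = 1.2.

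| Exercise v control | Noncentrality | Power |
|---|---|---|
| 20 v 20 | 3.79 | 0.96 |
| 12 v 20 | 3.29 | 0.89 |
| 6 v 20 | 2.58 | 0.70 |

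The control arm is held at 20 to isolate the effect of the attendance rule.

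**5. A tolerance closer to the control rule.** Two weeks is four sessions, so less than two weeks' worth missed means at most three missed, or at least 21 of 24. The binomial probability of 21 or more is 0.786 at p = 0.90 and 0.970 at p = 0.95, that is, 15.7 and 19.4 of 20.

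**The case against.** **The size of the set is a forecast.** This stands. The documents give no attendance rate, and absences tend to cluster within patients, which leaves more perfect attenders at the same average. The intervention description asks only for 48 hours between sessions, so making up a missed session is not ruled out. Either would retain more exercise patients than step 2 shows. The inequality of the two criteria needs no such assumption.

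**Controls would be lost too.** This also stands. A reader might picture a few exercisers set against almost the whole control arm. At 90% weekly adherence, however, about a third of controls would go as well. The gap between arms remains large, but it is not a comparison with an intact control arm.

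**The power loss can be overstated.** If 0.6 SD is taken as the difference in change itself, power at 6 v 20 is about 24%, which looks like a collapse. The same test with all 20 v 20 reaches only about 46%, so most of the distance from the planned 90% comes from the effect scale and not from this rule.

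**Three stronger readings are not supported.**

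- A reader might infer that the rule keeps controls who take up resistance training. The article does not define the lifestyle goals or what counts as poor adherence, so this cannot be known from it.
- A reader might infer that per-protocol has equal standing with intention-to-treat. The article says both will be done and ranks neither; a ranking may be set in a plan not shown.
- A reader might take bias in favour of exercise as established. It is plausible, but nothing in the documents demonstrates its direction. Blinded scoring of the apnea-hypopnea index protects the measurement but does not undo selection of who is analysed.

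**Conclusion.** The point holds for the per-protocol set. The criteria are unequal in strictness (24 of 24 sessions against less than two weeks of lapse) and in source (staff record against self-log), and this follows from the text alone.

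The numerical consequence is conditional. With independent sessions and attendance of 90% to 99%, between 1.6 and 15.7 of 20 exercise patients would be expected to remain, against 13.2 to 19.9 controls at the same weekly adherence. Even the top of the exercise range is just under the 16 per group that the plan calculated. Per-protocol power on the plan's implied 1.2 SD effect would fall from about 96% to 89% or 70% at 12 or 6 exercise patients. Those power figures rest on the assumed correlation of 0.5. Selection bias is a real risk, plausibly favouring exercise, but its direction and size are not shown.

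The intention-to-treat analysis is untouched, so the damage is confined to one analysis set. The rule should be changed, but it does not threaten the trial's main comparison.

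**What to change.** Before any analysis, replace the 24-of-24 criterion for the per-protocol set with a tolerance comparable to the control rule. For example, count an exercise patient as per-protocol with at least 21 of 24 sessions, meaning less than two weeks' worth missed. State that the per-protocol result is supportive of intention-to-treat.

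This takes a sentence or two in the analysis plan and alters only who enters one analysis set; the training schedule stays as it is. Enrolment was still under way when the article was submitted and all analyses are held until the end of the study, so the change can be made without knowledge of results.

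There are two costs. The per-protocol estimate would then refer to slightly less than full attendance. The match with the control rule is also only approximate: three missed sessions could fall in three different weeks and still pass, whereas controls are judged by the week. The difference in source, staff record against self-log, remains and should be mentioned when the result is reported.

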### Assessment of outcomes

#### Apnea-hypopnea index

Out-of-center polygraphy will assess the presence and severity of sleep apnea. Portable type III polysomnography monitors (Embletta Gold III, Embla, Broomfield, CO, USA; or SomnoCheck Effort, Weinmann, Hamburg, Germany) will be employed to evaluate: (1) chest effort, (2) abdominal effort, (3) oximetry, (4) nasal airflow, and (5) position, as previously described [48]. Apnea and hypopnea events, respiratory effort related arousals (RERAs), and the apnea-hypopnea and respiratory disturbance index will be reported according to the rules of the American Academy of Sleep Medicine (AASM) [49]. The AHI will define the diagnosis of sleep apnea. Polysomnography will be performed before and after 12 weeks using the same polygraph monitor on both occasions.

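### The two-visit time-by-group GEE is an unadjusted change-score comparison; adjusting for baseline AHI is nearly free, with a modest gain for the primary outcome

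*Protocol article*

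**What the plan says.** The Abstract (Methods/design) defines the endpoint: "The primary outcome measure of the study will be the change in apnea-hypopnea index". The Apnea-hypopnea index section gives two measurements: "Polysomnography will be performed before and after 12 weeks using the same polygraph monitor on both occasions". The between-group method is in Statistical methods: "Generalized estimating equations (GEE) will be used to detect differences between exercise and control groups and time*group interaction".

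Baseline values appear in one other place in that section: "The significance of the differences between groups, at the baseline, will be tested by the Student *t* test and chi-squared test". These tests describe the arms and do not bring baseline AHI into the model. No section names baseline AHI or any other covariate, or constrains the arms to a common baseline mean.

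The Sample size section uses the matching design of two groups and two assessments: "the sample size calculated for analysis of variance with repeated measures would be 16 patients in each group". The total is raised to 40, in two equal groups, to allow for losses. Eligibility requires a baseline AHI of 20 to 50 events/h. Statistical methods also calls for a natural-log transformation of dependent variables that are not normally distributed.

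**The concern.** With one measurement before treatment and one after, the term that carries the treatment effect subtracts each patient's full baseline value. That is the best use of baseline only if the regression slope of 12-week AHI on baseline AHI is 1. Single-night AHI varies, so a slope below 1 is to be expected. The change score then over-corrects: the arm that starts higher by chance appears to improve more.

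Two things are at stake. The estimate is less precise than the collected data allow. Also, in the one trial that will be run, a chance baseline difference between arms of 20 feeds partly into the estimate. Both can be avoided without new data.

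**Working it through.** **1. The plan's own figure.** Inputs from Sample size: two groups, two assessments, 0.6 SD, 90% power, alpha 5%. The pre/post correlation ρ is not stated; assume 0.5. Take f = 0.6/2 = 0.3. For the repeated-measures interaction with N = 32 and m = 2:

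λ = f² × N × m / (1 − ρ) = 0.09 × 32 × 2 / 0.5 = 11.52, on 1 and 30 df, giving power 0.907.

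This reproduces 16 per group. The between-groups version of the same test would need N = 90. The sizing therefore matches the interaction, the contrast discussed here.

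**2. What the interaction estimates.** In a model with group, time and their product, the product term is (12-week mean − baseline mean) in the training arm minus the same in the control arm. A GEE fitted to one simulated data set of 16 per arm gave −0.3928 under independence and under exchangeable working correlation. The raw difference in mean change was also −0.3928.

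**3. General formulas.** Let Sb and Sy be the within-arm SDs at baseline and 12 weeks, and β = ρ × Sy/Sb the regression slope.

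- Change-score variance: Sy² + Sb² − 2βSb²
- Baseline-adjusted variance: Sy² − β²Sb²
- Difference between them: Sb²(1 − β)², never negative
- Expected shift of the change contrast for a chance baseline difference D: −(1 − β) × D

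**4. Equal SDs (best case).** Here β = ρ, and the variance ratio is (1 − ρ²) / [2(1 − ρ)] = (1 + ρ)/2.

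| ρ (assumed) | adjusted / change variance | saving |
|---|---|---|
| 0.3 | 0.65 | 35% |
| 0.5 | 0.75 | 25% |
| 0.7 | 0.85 | 15% |
| 0.9 | 0.95 | 5% |

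In 20,000 simulated trials of 16 per arm at ρ = 0.5 with a true effect of −0.6 SD, both methods averaged about −0.60. The SE was 0.352 for change and 0.312 for the adjusted estimate. The variance ratio of 0.785 includes the cost of estimating the slope. The estimate's slope on chance imbalance was −0.49 for change and about 0 after adjustment.

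**5. The primary outcome under the entry window.** The 20 to 50 limits restrict baseline AHI only; 12-week AHI is free to spread. As an illustration, assume baseline AHI is uniform over the window, so Sb = 30/√12 = 8.66 and Sb² = 75, and assume β = 0.5. The absolute saving is 75 × 0.25 = 18.75.

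- If Sy = Sb: change variance 75 + 75 − 75 = 75; saving 18.75/75 = 25%.
- If Sy = 2Sb (Sy² = 300): change variance 300 + 75 − 75 = 300; saving 18.75/300 = 6.25%. The correlation here is β × Sb/Sy = 0.25.

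Simulations of log-normal AHI cut to 20–50 at entry (assumed medians 15–30, log-scale SD 0.5–0.8, correlation before truncation 0.5–0.85) gave savings of about 0 to 14%.

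**6. Chance imbalance in events/h.** With 20 per arm and the same Sb, the SE of the baseline difference is 8.66 × √(2/20) = 2.74. A one-SE imbalance shifts the change contrast by 2.74 × 0.5 = 1.37 at β = 0.5, or 2.74 × 0.08 = 0.22 at β = 0.92. The simulations gave about 0.2 to 1.4. Against the average effect of seven events/h cited in Background, that is 0.2/7 = 3% to 1.4/7 = 20%.

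**The case against.** The strongest reply is that the plan is sound and consistent as written. Change in AHI, two assessments, a repeated-measures sample size and a time-by-group GEE fit together. The type I error is unaffected by this choice. The interaction already subtracts the raw baseline difference, so only a (1 − β) share remains. All of this stands, and it makes the point one of efficiency.

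It can also be said that the article does not rule covariates out, and that a covariate list may sit in an analysis plan that is not shown. This is fair as far as it goes: the lack of adjustment is read from the absence of any named covariate. But the article does fix the contrast, and as fixed it is a comparison of raw changes.

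Three stronger readings are tempting, and the documents do not support them.

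- *Selecting patients on a single-night AHI biases the comparison.* Regression toward usual levels is expected, but equally in both randomised arms, so it cancels from the contrast. Only chance imbalance matters.
- *The window lowers the correlation and so raises the gain.* That follows only if the two SDs stay equal. Truncating baseline makes them unequal, and step 5 shows a lower correlation with a smaller proportional saving.
- *The trial is short of power, so the loss is serious.* Power figures of 38% or 46% for a 0.6 SD difference come from a separate question, how that effect size was entered in the sample-size calculation, and should not be counted again here. On the effect that reproduces 16 per group, power is already 0.907; adjustment would bring it to about 0.96 even with equal SDs.

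**Conclusion.** The point holds as an inexpensive improvement to a valid analysis. The planned interaction is, with complete data, an unadjusted change-score comparison. It is unbiased on average but less precise than a baseline-adjusted one, and it retains a (1 − β) share of any chance baseline difference with reversed sign.

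For the primary outcome the likely variance saving is about 0 to 14%, and a one-SE imbalance is worth roughly 0.2 to 1.4 events/h. These ranges rest on assumed log-normal AHI distributions, because the protocol gives neither SDs nor a pre/post correlation. A reader might apply the 25% saving to AHI directly; the entry window makes that an untruncated best case. It applies more directly to the continuous secondary outcomes, which are not used to select patients, with smaller gains where pre/post correlation is high. In no scenario examined was adjustment materially worse.

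**What to change.** Make the primary analysis a linear model of 12-week AHI on group, adjusted for baseline AHI, and report the adjusted mean difference with its 95% CI. A longitudinal model with the group means constrained to be equal at baseline is an acceptable alternative. Its covariance should allow different variances at the two visits. In a GEE with independence working correlation, the constraint alone would reduce the contrast to a plain comparison of 12-week means.

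If AHI is log-transformed under the rule in Statistical methods, adjust for log baseline AHI and report a ratio of geometric means with its 95% CI. Treat the continuous secondary outcomes in the same way.

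The cost is one degree of freedom and a few lines of analysis wording, with no new visits or data. The article places all analyses at the end of the study and describes enrolment as ongoing, so on the documents the change would precede any analysis.
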